### The current study

This protocol paper describes the development of an intervention which makes use of the Headspace mindfulness meditation app for smartphones, tablets and web browsers to evaluate its effects on executive control, critical thinking and key thinking dispositions as well as the real-world outcomes of critical thinking. This intervention was developed in order to test, in the most rigorous way available, hypotheses developed as a result of careful review of the literature on the effects of mindfulness on self-regulation and cognitive abilities and studies carried out previously by the authors suggesting that mindfulness may facilitate more effective critical thinking. The rationale for this intervention relies heavily on a specific type of dual-process theory known as the default-interventionist theory of higher-order cognition [34], which can be used as a framework to integrate research on the effects of mindfulness on attention, executive function and self-regulation of behaviour in general and research on the self-regulation of higher-order cognition, such as critical thinking [17].

In summary, the central research question here is: does regular mindfulness meditation practice facilitate critical thinking through the enhancement of executive function? To answer this, the proposed study aims to ascertain whether a 6-week online mindfulness meditation intervention increases trait mindfulness, executive function, critical thinking performance and endorsement of key critical thinking dispositions to a greater extent than an active-control sham meditation condition. The hypotheses to be tested can be seen in Table 1. This aim will be achieved by testing these hypotheses using the measures and analyses described in the next section. It is also intended to investigate the role of executive function in mediating the predicted positive relationship between mindfulness and critical thinking performance. Finally, the study aims to explore the participants’ experiences of taking part in an online mindfulness meditation intervention and the real-world outcomes they perceived.

**Table 1 Tab1:** Study hypotheses

Outcomes	Variable	Measure		Hypothesis	Analysis
Primary	Mindfulness	Five Facet Mindfulness Questionnaire	1	Mindfulness will increase more for the mindfulness meditation (MM) group than for the sham meditation (SM) group from t_1_ to t_4_	Mixed ANOVA

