	Critical Thinking	Halpern Critical Thinking Assessment^1^, Heuristic and Biases items^2^	2	Critical thinking will increase more for the MM group than for the SM group from t_1_ to t_4_ *(a* ^*1,2*^ *)* and this effect will be moderated by baseline endorsement of thinking dispositions *(b* ^*1,2*^ *)*	Mixed ANOVA, ANCOVA
	Thinking Dispositions	Actively Open-minded Thinking^1^, Need for Cognition^2^	3	Endorsement of critical thinking dispositions will increase more for the MM group than for the SM group from t_1_ to t_4_ *(a* ^*1,2*^ *)*	Mixed ANOVA
	Executive Control	Sternberg Working Memory Task	4	Executive control will increase more for the MM group than for the SM group from t_1_ to t_4_ *(a)* and this increase will mediate the relationship between levels of mindfulness and critical thinking performance following the intervention *(b)*	Mixed ANOVA, SEM
Secondary	Wellbeing	Warwick-Edinburgh Mental Wellbeing Scale	5	Wellbeing will increase and negative affect will decrease more for the MM group than for the SM group from t_1_ to t_4_	Mixed ANOVA
	Positive Affect and Negative Affect	Positive Affect and Negative Affect Schedule subscale	6	Positive affect will increase more for the MM group than for the SM group from t_1_ to t_4_ *(a)*	Mixed ANOVA
	Real-world Outcomes	Real-world Outcomes Inventory	7	Negative real-world outcomes will decrease more for the MM group than for SM group from t_1_ to t_4_	Mixed ANOVA
Manipulation Checks	Meditation Quality	Practice Quality-Meditation	8	Meditation quality will be positively associated with increases in mindfulness *(a)*, executive control *(b)* and critical thinking *(c* ^*1,2*^ *)* and meditation quantity *(d)*, task enjoyment *(e)* and task difficulty *(f)* and it will be higher in the MM group and across time.	Correlation, Mixed ANOVA
	Meditation Quantity	Total Minutes Spent Meditating	9	Meditation quantity will be positively associated with increases in mindfulness *(a)*, executive control *(b)* and critical thinking *(c* ^*1,2*^ *)* and meditation quality *(d)*, task enjoyment *(e)* and task difficulty *(f)* and will not differ across time or groups.	Correlation, Mixed ANOVA

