	Task Enjoyment	Technology Acceptance Model Questionnaire subscale	10	Task enjoyment will be positively associated with increases in mindfulness *(a)*, executive control *(b)* and critical thinking *(c 1,2*) and meditation quality *(d)*, meditation quantity *(e)* and task difficulty *(f)* and will not differ across time or groups.	Correlation, Mixed ANOVA
	Task Difficulty	Technology Acceptance Model Questionnaire subscale	11	Task difficulty will be positively associated with increases in mindfulness *(a)*, executive control *(b)* and critical thinking *(c 1,2*) and meditation quality *(d)*, meditation quantity *(e)* and task difficulty *(f)* and will not differ across time or groups.	Correlation, Mixed ANOVA
	Intervention Acceptability	Items from Kirkpatrick et al. [60]	12	Intervention acceptability will be positively associated with increases in mindfulness *(a)*, executive control *(b)* and critical thinking *(c* ^*1,2*^ *)* and meditation quantity *(d)*, task enjoyment *(e)* and task difficulty *(f)* and it will be higher in the MM group but will not differ across time.	Correlation, Mixed ANOVA
	Attrition	No. of participants lost from baseline to t_4_	13	Attrition will be negatively associated with meditation quality *(a)*, meditation quantity *(b),* task enjoyment *(c)* and task difficulty *(d)* and will not differ across time or groups.	Correlation, Mixed ANOVA

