### Recruitment and randomisation

Students enrolled in psychology will be invited to participate and on acceptance of this invitation will fill out the screening questionnaire online. Those that satisfy the inclusion criteria will be selected to take part in the intervention and will be randomised to either the mindfulness meditation group or the sham meditation group with a 1:1 ratio. Block randomisation will be employed using a fixed block of 6 [50]. Unique Headspace access codes corresponding to the two conditions will be provided to the researcher. These will be labelled Condition A and Condition B and only after analysis will the nature of these conditions be revealed to the researchers by Headspace. Therefore both participants and researchers will be blinded. However, blinding can be readily undone on a participant-by-participant basis if necessary.

Potential participants will be invited to take part by email and through advertisements on social media. Announcements regarding the study will also be made by the researchers in lectures attended by 1st year and 2nd year undergraduate psychology students.

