### Primary outcome measures

#### Halpern Critical Thinking Assessment (HCTA; [51])

The HCTA involves 25 real-world situations with closed and open questions based on these situations. These situations involve medical research, social policy analysis and other types of problems encountered in everyday life. Five domains of critical thinking are assessed using the HCTA: Verbal reasoning, argument analysis, thinking as hypothesis testing, likelihood and uncertainty, and decision-making and problem-solving. The test includes 5 sets of questions (one open and one closed) for each of these domains. The scoring guide provides answers for forced-choice questions while open-ended questions are graded according to specific grading prompts (for more detail see [61]). Greater scores are awarded to more accurate and comprehensive answers and total scores can range from 0 to 194 [51]. The internal reliability of the HTCA tends to be adequate [51, 61]. The HCTA has been shown to be sensitive to change in previous intervention studies comparing methods of critical thinking instruction [62, 63].

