### Heuristics and Biases items [5]

This series of standard items assessing cognitive biases is included as there is evidence that these assess an aspect of critical thinking not captured by traditional measures [5]. These items assess participants’ ability to deal with problems involving causal base rates, noncausal base rates, the law of large numbers, regression to the mean, the gambler’s fallacy, conjunctions, covariation, Bayesian reasoning, framing and probabilistic reasoning (for full details of the items see [5]). Each of these items will be scored as either correct (1) or incorrect (0). Though these are not representative of a unidimensional construct, it has been shown to be useful to aggregate scores on these items [5].

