### Data management and access

This data management plan has been created using the UCD Data Management Checklist [70]. The data will be saved online through Inquisit (the Sternberg Memory Task) and Surveygizmo (all other tasks and questionnaires). This data is only accessible by the first author. When these data are collated, the second author will also have access to the relevant data files. The data will be saved in both .csv and .sav formats. These files will be stored in encrypted Dropbox folders. A detailed logbook will be created to complement these files. We do not currently have ethical approval to share these data. In accordance with the NUI Galway data retention policy, these data will be retained for 5 years at the NUI Galway School of Psychology (as well as being backed up on Dropbox) and anonymised by replacing student ID numbers and names with randomly generated subject ID numbers.

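### The only researcher blinding stated is a shared A/B label that the week 2 and 4 data could decode; grading open HCTA answers without the label would close the gap cheaply

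*Protocol article*

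**What the plan says.** On blinding, the Recruitment and randomisation section says "Unique Headspace access codes corresponding to the two conditions will be provided to the researcher", and then "These will be labelled Condition A and Condition B and only after analysis will the nature of these conditions be revealed to the researchers". It concludes from this that participants and researchers are both blinded. The Discussion counts the double-blind design among the study's strengths on the same basis.

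On the outcome, The current study frames the central question as "does regular mindfulness meditation practice facilitate critical thinking through the enhancement of executive function". Table 1 tests critical thinking (hypothesis 2) with two measures, the HCTA and the Heuristics and Biases items. The HCTA has one open and one closed question in each of 25 situations. In the HCTA section, "open-ended questions are graded according to specific grading prompts", and fuller and more accurate answers earn more marks. The Heuristics and Biases items are simply right or wrong.

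On the data that could reveal the label, Table 1 predicts of meditation quality that "it will be higher in the MM group and across time" (hypothesis 8), and of intervention acceptability that "it will be higher in the MM group but will not differ across time" (hypothesis 12). The Design and Data collection sections place both measures at weeks 2 and 4.

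On access, Data management and access first limits the stored data to the first author. It then adds: "When these data are collated, the second author will also have access to the relevant data files".

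**The concern.** A label shared by a whole arm differs from an individual code. Once somebody works out what A means, every participant's allocation is known. The same feature sits badly with the statement in Recruitment and randomisation that blinding can be undone one participant at a time: telling a researcher who holds the labels what one participant received tells that researcher what everyone received.

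Such a label serves well for running the ANOVAs. It is a weaker safeguard where a person must decide how many marks a written answer deserves. The protocol itself predicts that two measures taken before the final assessment (T4) will separate the arms in a known direction. If the grader has formed a view on which label is mindfulness, any generosity towards that label at T4 adds to the time by group interaction, which is the test of hypothesis 2.

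**Working it through.** **Figures in the plan.** The protocol gives no figure for blinding or grading. The only figure borrowed is the target of 30 per group. It is the rounded-up form of a G*Power result of 56, which reproduces as the between-groups test of a repeated-measures ANOVA with f = 0.25, 6 measurements and correlation 0.3: noncentrality = 0.25² × 56 × 6 / (1 + 5 × 0.3) = 8.4, power 0.81. Nothing below depends on whether that was the right test.

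**Step 1: order of events.**
- Before the intervention (T1): baseline HCTA answers.
- Weeks 2 and 4: quality and acceptability.
- Week after the intervention (T4): final HCTA answers.
- After analysis: meaning of A and B revealed.

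The potentially revealing data therefore exist before any T4 answer can be graded. The article does not fix when grading or by-label summaries take place.

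**Step 2: how well would one comparison of means identify the label?** If the mindfulness arm truly scores d standard deviations higher on a check, the arm with the higher observed mean is mindfulness with probability Φ(d × √(n/2)), for n per arm. With n = 30, √(n/2) = 3.873. All d values are assumptions.
- d = 0.2: Φ(0.775) = 0.78
- d = 0.3: Φ(1.162) = 0.88
- d = 0.5: Φ(1.936) = 0.97
- d = 0.8: Φ(3.098) > 0.99

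With 24 per arm (30 less 20%), d = 0.5 gives Φ(0.5 × √12) = Φ(1.732) = 0.96. Averaging weeks 2 and 4 replaces d by d / √((1 + r)/2), where r is the correlation between waves. For r from 0.3 to 0.7 and n = 30, the result is 0.98 to 0.99 at d = 0.5 and 0.80 to 0.83 at d = 0.2.

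These are probabilities that a guess is right, not that a test is significant: at d = 0.5 and n = 30, a two-sided 5% t-test has power of only 0.49. If the predictions are false and d = 0, the guess is right half the time.

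**Step 3: what leniency could do (purely illustrative).** The documents give neither the share of the 194 HCTA points that comes from open answers nor an SD. Assume half the points (97) and an SD of 15 to 25.
- Leniency of 2% of the open points in one arm at T4: 0.02 × 97 = 1.94 points, or 0.08 to 0.13 SD.
- Leniency of 5%: 0.05 × 97 = 4.85 points, or 0.19 to 0.32 SD.

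The standard error of the interaction in SD units is √(2(1 − ρ)) × √(2/30), where ρ is the correlation between T1 and T4. For ρ = 0.3 it is 0.306; for ρ = 0.7 it is 0.200. With no true effect, a shift of 0.2 SD raises the two-sided 5% false-positive rate to 0.10 (ρ = 0.3) or 0.17 (ρ = 0.7). A shift of 0.3 SD raises it to 0.17 or 0.32. No document suggests that leniency of any such size would occur.

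**The case against.** The strongest reply is that this is a condensed article. Who grades, and what graders see, normally belongs in the full protocol, and the HCTA section refers the reader elsewhere for grading detail. The harm also needs a chain of events that the text does not state: the grader has the labels, someone compares the checks by label before grading, the predictions are true, each answer can be tied to its label, and marking then becomes lenient. The labels attach to Headspace codes while the answers sit in the survey system, and nothing says that the two are joined before grading. Table 1 predicts no arm difference in meditation quantity, enjoyment or difficulty. Both arms hear the same narrator in the same app. Random subject numbers replace names and student IDs once data collection ends, which is compatible with de-identified grading.

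Most of this stands and limits the point. The prompts restrict discretion, and the closed HCTA answers and right-or-wrong heuristics items are little exposed. What remains is not a complaint about missing detail. The article states a mechanism and draws a double-blind conclusion from it, and for graded answers that conclusion is only as secure as the label.

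A reader might go further in three ways that the documents do not support:
- That grading is in fact unblinded. No section says that graders see the label.
- That any leniency would be beyond detection or repair. Data are kept for five years, so a masked rater could regrade the answers, and open scores could be compared with closed scores.
- That a grader who knows T1 from T4 is a problem in itself. A shift by time point alone affects both arms equally and cancels in the interaction; it matters only together with the label.

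**Conclusion.** This is a cheap improvement. The stated researcher blinding rests on one shared label, and the protocol's own predictions supply a plausible way to decode it before T4 answers are graded. Given a true difference in the predicted direction and someone who compares the labels, one check points to the mindfulness label with probability from about 0.78 (d = 0.2) to 0.97 (d = 0.5) at 30 per arm. The size of any resulting bias cannot be estimated from the documents, and the SD shifts above only illustrate the scale.

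Exposure is confined to the open part of one of two critical thinking measures, and critical thinking is one of several listed primary outcomes. It is nevertheless the outcome in the central research question, which makes the safeguard worth stating.

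**What to change.** State in the protocol that all T1 and T4 open-ended HCTA answers are exported to one file without participant ID, A/B label or time point, put in random order, and graded. Lock the grades before any outcome or manipulation-check variable is summarised by label. Merge arm and time back only after the lock. Time point is removed along with the label because the two together would let a grader influence change scores.

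The cost is a short export-and-shuffle script and a sentence of text, with no additional grader and no change to design, measures or analysis. The one drawback is delay: baseline answers cannot be graded until T4 collection is complete.

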### Intervention

Intervention materials will be delivered via Headspace, a commercially available application which runs on all major smartphones, tablets and web browsers. The Headspace meditation scripts are designed by an individual with Buddhist monastic training who guides users through mindfulness meditations and key concepts related to mindfulness meditation using both audio and visual materials. In order to participate, individuals are required to have access to a smartphone or desktop computer with Internet access. Headspace makes meditating accessible by combining technology and simple techniques that are designed for new meditators. Participants can practice at any time of day wherever they prefer. Headspace offers straightforward, guided, bite-sized mindfulness training that is non-religious. We have signed guarantees with Headspace that participant data collected through Headspace will never be sold, distributed, or publicised (except anonymously in scientific publications with Headspace having no involvement in the conduct, analysis, or reporting of the research in any way).

Participants will be sent an email introducing Headspace and describing the sign-up process. To get started, participants are required to register on headspace.com using their name and email address. Each participant will be given a unique code providing free access to Headspace for the duration of the study. After registering, participants may begin meditating straight away.

The proposed intervention is 6-weeks in length. All participants will be encouraged to practice meditation/sham-meditation daily for the course of the 6-weeks by listening to each of the 30 ten-minute guided sessions which they will access through the Headspace app. The nature of the sessions they can access depends on the group they are assigned to.

### Experimental condition

Participants in the experimental condition will gain access to 30 sessions of guided mindfulness practice. These sessions introduce the concept and practice of mindfulness training and each session gradually builds on the previous one. The sessions are guided by [name], a trained Buddhist monk who is also a registered meditation consultant with the UK Health Commission. Each session begins with the participant begin instructed to sit, close their eyes and take deep breaths. Following this, participants are guided through mental body scan exercises intended to cultivate a mindful state which involve practicing focusing attention on present-moment sensations in the body without emotionally elaborating on these sensations. Gradually participants learn to re-direct their attention when the mind wanders and to broaden their present-moment awareness to all current internal and external stimuli. Towards the end of the course of sessions, participants are encouraged to apply this type of awareness to everyday activities.

### Active-control condition

Participants in the active-control condition will gain access to 30 sessions of guided sham meditation practice. These sessions discuss meditation and introduce breathing exercises under the guise of mindfulness practice. However, specific instructions for how to pay attention to the breath or other stimuli are not given. Instead, participants are encouraged to sit quietly, with their eyes closed and every few minutes they are reminded to take deep breaths as they sit in meditation. These sessions are also guided by [name] and accessed in exactly the same way as content in the experimental condition. This approach was taken as it controls for both physiological relaxation and expectations regarding meditation. Other approaches used in previous studies have only controlled for one of these [39]. For example, progressive muscle relaxation only controls for physiological relaxation, while mind wandering inductions only control for expectations regarding meditation. These approaches did improve on previous attention-only and audiobook controls and all of these are a significantly better approach than waitlist controls when possible [10].

### Adherence

Objective adherence data will be collected through the Headspace accounts of the participants. These data will include both the number of sessions initiated and the number of minutes spent listening to the guided sessions. One email and one text message per week will be sent to participants to encourage them to adhere to the intervention.

### Data collection

Primary and secondary measures will be taken at baseline and following the end of the intervention (see Table 2). In terms of primary outcome measures, we will assess critical thinking using the Halpern Critical Thinking Assessment [51] and items from the Heuristics and Biases literature [5], mindfulness with the Five Factor Mindfulness Questionnaire (FFMQ;[52]), thinking dispositions with the Need for Cognition scale [53] and the Actively Open Minded thinking scale [8] and executive function with the Sternberg working memory task [54] presented on Inquisit software [55]. Objective measures of meditation adherence (no. of sessions initiated and completed and no. of minutes spent meditating) will be gathered through the Headspace app. Secondary measures will assess effects on wellbeing in order to compare with previous studies employing Headspace. The Positive Affect and Negative Affect Schedule [56] and the Warwick-Edinburgh Mental Wellbeing Scale [57] will be used. All of the measures except the Sternberg Working Memory Task will be presented using SurveyGizmo. Data Collection will take place during the week preceding the start of the intervention in the PC Suites of the School of Psychology at NUI Galway. Three sessions will be scheduled in order to facilitate attendance at different times, each of which will be able to accommodate up to 30 participants comfortably. A break with food and refreshments will be given half way through the procedure. This data collection approach will be repeated during the week following the end of the intervention.

Manipulation checks will be carried out during weeks 2 and 4 of the intervention and will focus on mindfulness meditation quality and task expectations, enjoyment and difficulty. Mindfulness meditation quality will be assessed using the 6 item Practice Quality- Mindfulness questionnaire [58] while task expectations, enjoyment and difficulty will be assessed using the Technology Acceptance Questionnaire [59] and Intervention Acceptability items [60]. These questionnaires will be administered online using SurveyGizmo through a link which will be distributed by email.

